### Blinding

The trial will be an assessor-blinded study where the outcome assessor, who will be a physiotherapist, will be blinded to group allocation. The principal investigator and participants will be informed of the group allocation given the nature of the interventions. Furthermore, the statistician who will perform data analysis would be unaware of the existence of treatment groups.

### Intervention

VR-based balance training will be provided by the Nintendo Wii Sports Resort (Nintendo Co. Ltd., Kyoto, Japan). It uses a central game console connected to a 127-cm (50-inch), wall-mounted television screen. Navigation is via the handheld remote control in the gaming environment. The choice of games was based on the similarity between the training and real-life conditions and based on previous research using the Nintendo Wii in training sitting balance in various neurological populations. During the first session, the therapist will demonstrate the game controls and instructions to ensure that the participants understand how to control the system. Furthermore, the therapist will offer verbal and manual guidance to all participants to help them learn the best strategies to reach the highest scores in each game. An equal number of rounds per exercise will be presented to the participants during each training session. Rest would be allowed and training would be resumed afterward if the participant declared fatigue (Table 3).

**Table 3 Tab3:** Description of games using Nintendo Wii Sports Resort program

Game	General description
Table tennis	Sitting with the Nintendo Wii remote in hand, subjects must hit the ball in the plane of the table and prevent it from falling off the table in a game of 6 points
Swordplay	Sitting with the Nintendo Wii remote in hand, subjects must slice out different objects shown on the screen following directional cues marked on them
Bowling	Sitting with the Nintendo Wii remote in hand, subjects mimic the motion of bowling by moving their arms sideways and performing a free, fluid throwing motion aimed at knocking down all the pins in a simulated bowling lane
Golf	Sitting with the Nintendo Wii remote in hand, subjects mimic; there is a map and speed and angle chart on the screen, seeing which they must target the ball in the hole by hitting it with the stick by managing the force, and the fewer the number of hits, the higher the score
Frisbee	Sitting with the Nintendo Wii remote in hand, subjects visualize it as a frisbee and try to throw it toward a marked arrow displayed on the screen, with the goal of landing as close to the arrow as possible to achieve the highest score
Canoeing	Sitting with the Nintendo Wii remote in hand, subjects mimic the motion of paddling by changing the direction of the remote to navigate straight ahead with fluid hand movements. The objective was to reach the final target within 1 min while maintaining a steady rhythm and control

Participants in the VR-SES group will receive SES while performing virtual reality-based balance training. SES will be delivered using a transcutaneous electrical nerve stimulation (TENS) machine (HMS DigitensII) that uses surface self-adhesive stimulation electrodes placed on the subject’s skin corresponding to the muscles targeted. The key muscles that will be targeted are the erector spinae.

Electrodes will be placed bilaterally on the muscle belly of the erector spinae in the thoracolumbar region, along the orientation of the muscle fibers at the T6 and T12 vertebral levels (Fig. 2). SES will be applied continuously throughout the entire 30-min VR training session.

**Fig. 2 Fig2:**
[figure not shown]
Schematic representation of electrode placement for sensory electrical stimulation (SES) over the erector spinae muscles

The pulse width will be 200 μs, and the pulse frequency will be 100 Hz. The current levels will be separately selected such that the participant feels the stimulation at the level (suprasensory threshold) without having the stimulated muscles contract due to the stimulation [27]. The suprasensory threshold will be determined by gradually increasing the stimulation intensity until the participant first perceives the stimulus, and then further increasing it to a clearly perceptible, comfortable level without any visible or palpable muscle contraction, as confirmed by the therapist’s observation. This process will be followed for all participants, and all sessions will be administered by a single trained therapist to ensure consistency of the sessions. Adverse events will be monitored and reported, if any.

### Progression and feedback

The initial difficulty will be adjusted for each participant based on their performance during the familiarization session. Progression of task difficulty will be based on predefined game-specific performance indicators generated by the Nintendo Wii, including in-game scores, task completion, and stage progression. Participants will receive concomitant visual and auditory feedback regarding task performance when movements are accurately performed, as learning is also affected by performance-related feedback. Participants will also receive negative feedback about their performance when they use compensatory strategies while playing games on the Nintendo Wii verbally by the supervising therapist.

### Termination criteria

The intervention will be terminated if any kind of unusual uneasiness is reported by the participants. Participants will be instructed to report any adverse events experienced during or after the intervention throughout the study period to the principal investigator or research team. The intervention session will be discontinued if the participants report discomfort, pain, or excessive fatigue during the session.

### Adherence

The adherence of the participants recruited in the study will be monitored by documenting the details of sessions attended. Participants in all groups will receive VR-based balance training, which may positively influence adherence and reduce attrition rates, as all groups are likely to feel engaged in an active intervention.

The participants will be permitted to increase the training duration by 1 week, keeping in mind the “intention-to-treat” analysis principle if the participants are unable to complete the total number of sessions within the stipulated 4 weeks. Also, the authors will fully report the type, extent, and pattern of missing data throughout the study (Table 4).

**Table 4 Tab4:**
[figure not shown]
Protocol for experimental (VR-SES) and control (VR) group

### Outcome variables

Modified functional reach test (mFRT): The participant sits in a standard wheelchair, with hips, knees, and ankles positioned at approximately 90° and feet supported. Initial reach is measured against a yardstick mounted on the wall, and then the maximum forward reach is measured using the ulnar styloid process as a landmark. The difference is the measure of functional reach in a sitting position. Each participant performs three trials, and the average of these measurements is used for analysis. It has been reported to have good to excellent reliability, with intraclass correlation coefficient (ICC) values ranging from 0.78 to 0.99 [28].

Star test: The ProKin trunk sensor platform (ProKin PK252; TecnoBody Inc., Dalmine, Italy) will be used. The participant sits on the ProKin 252 multiaxial platform with their back straight, hip and knee flexed at 90°. During the star test, a target appears in different directions on the screen. The participant has to reach the target on a given path by shifting his weight toward that direction. The shifting of weight is done by moving the multiaxial platform in different directions. After a series of such movements, the Tecnobody software provides a final report in terms of total area covered during the test. It has been found that the ProKin device is reliable and valid for assessing standing balance in individuals with iSCI. Test-retest reliability was found to be moderate to excellent (ICC = 0.64–0.93) [29].

International SCI Quality of Life Data Set—version 1.0: It was developed as a brief QoL measure for use in clinical practice and research. It consists of three items for an individual to rate their satisfaction with life, physical health, and psychological health. Each domain is ranked on a 0–10 scale, where 0 indicates complete dissatisfaction and 10 indicates complete satisfaction. The tool has been reported to be both valid and reliable. The three items exhibited strong inter-correlations, ranging from 0.48 to 0.71. Furthermore, the scale demonstrated good internal consistency with a Cronbach’s alpha of 0.81, and item-rest correlations fell between 0.57 and 0.74 [30].

## Statistics

### Sample size

A priori sample size estimation was done using the G*Power 3 software (3.1.9.6, Heinrich-Heine-Universität Düsseldorf, Düsseldorf, Germany) by considering the mFRT as the primary outcome measure. The total sample size was calculated at 20 by using an *α* level of 0.05 and a power of 80%. The potential loss to attrition was estimated at 10%. Hence, the total sample size was 22.

### Statistical analysis

To check for selection bias, we will apply Pearson’s chi-square test for categorical variables and the Student *t*-test for numerical variables. This will be performed to know if the randomization process generated between each group of participants has homogeneous clinical and demographic characteristics before the intervention.

Continuous variables will be summarized as mean ± standard deviation for normal distribution and median ± interquartile range for non-normal distribution. The Shapiro-Wilk test will be used to determine the normality of data. In the case of normal distribution of data, we will analyze the intergroup comparison by applying a two-sample *t*-test. In case of skewed data, we will use the Mann-Whitney *U* test for the intergroup comparison. The intragroup comparison will be analyzed by repeated-measure analysis of variance (ANOVA) or Friedman’s test (if data is not normally distributed). The final statistical analysis will be performed using IBM SPSS Ver. 29.0 (IBM Corp., Armonk, NY, USA). This will be done based on the modified intention-to-treat principle, whereby each participant must complete > 75% (15 of 20 sessions) of planned exercise sessions. The principle of the “last observation carried forward” will be applied in the case of missing data for dropped-out individuals. The level of statistical significance is assumed at a *p *value < 0.05. No interim analysis will be conducted due to the short duration of the study. Formal stopping rules based on statistical criteria have not been defined. However, the trial may be terminated early upon recommendation of the IEC in case of safety concerns or unforeseen circumstances.

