### Patient and study design

An assessor-blind, parallel, two-group, randomized controlled trial with equal subject allocation (1:1) will be undertaken. A sample of 22 participants with iSCI will be recruited from the inpatient and outpatient rehabilitation departments of the Indian Spinal Injuries Centre, New Delhi, India. All participants will be provided with information sheets, and written consent will be obtained by the principal investigator before recruitment. The demographic details will be obtained, and the participants will be selected based on the eligibility criteria after neurological examination (Table 1).

**Table 1 Tab1:** Eligibility criteria

	Criteria
Inclusion criteria	Diagnosis of spinal cord injury > 6 months T6–T12 level of injury ASIA B, C, D Age between 18 and 60 years Ability to sit unsupported for 10 s and a minimum of 90° shoulder flexion
Exclusion criteria	Uncorrected hearing or visual impairment that interferes with the ability to perceive visual stimuli, follow verbal instructions, or safely participate in the virtual reality-based intervention Deformity of upper limb, any other psychiatric, neurological, or musculoskeletal impairment History of severe recent urinary tract infection or autonomic dysreflexia Refusal or inability to provide informed consent and inability to follow commands Additional exclusion criteria (sensory electrical stimulation group): 1. Pressure sores ≥ grade 2 at the site of stimulation according to National Pressure Ulcer Advisory Panel Classification 2. Cardiac pacemaker

The participants will be randomly assigned to any of the two groups—the virtual reality-based balance training along with sensory electrical stimulation (VR-SES) group and the virtual reality-based balance training (VR) group. Both groups will receive intervention sessions five times per week for 4 weeks.

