**Table 2 Tab2:**
[figure not shown]
Schedule of enrollment, interventions, and assessments according to the Standard Protocol Items: Recommendations for Interventional Trials guideline

*Abbreviations*: *VR-SES group* Virtual reality-based balance training along with Sensory electrical stimulation, *VR group* Virtual reality-based balance training, *mFRT* Modified functional reach test, *ISCoS Qol BDS V1.0* International Spinal Cord Society Quality of Life Basic Data Set Version 1.0.

Baseline assessments (T_0_) will be done before group allocation. Post-intervention assessments of both groups (T_1_) will be done after 4 weeks of intervention to detect potential long-term effects.

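### The analysis labelled modified intention-to-treat admits participants by session attendance, so the primary mFRT comparison is a per-protocol comparison that randomisation no longer protects

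*Protocol article*

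**What the plan says.** All references are to the protocol article.

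- **Statistical analysis, software:** "The final statistical analysis will be performed using IBM SPSS Ver. 29.0". The next sentence says that this analysis follows a "modified intention-to-treat principle, whereby each participant must complete > 75% (15 of 20 sessions) of planned exercise sessions". The article names no other analysis set.
- **Statistical analysis, missing data:** last observation carried forward "will be applied in the case of missing data for dropped-out individuals".
- **Adherence:** "The participants will be permitted to increase the training duration by 1 week", and this is done "keeping in mind the “intention-to-treat” analysis principle if the participants are unable to complete the total number of sessions".
- **Patient and study design:** "Both groups will receive intervention sessions five times per week for 4 weeks", which gives 5 × 4 = 20 planned sessions.
- **Table 2 notes:** the baseline assessment (T0) "will be done before group allocation"; the only later assessment (T1) follows the 4 weeks of intervention.
- **Termination criteria:** "The intervention will be terminated if any kind of unusual uneasiness is reported by the participants". A session also stops for discomfort, pain or excessive fatigue. Neither rule is limited to one arm.
- **Blinding:** the outcome assessor is blinded; participants and the principal investigator are not.
- **Sample size:** mFRT is the primary outcome, with α 0.05, power 80%, 20 participants, 10% attrition and a total of 22. No effect size, SD or sidedness is given.

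**The concern.** Randomisation makes the arms comparable at allocation. A set chosen by later attendance need not be comparable, because those who keep attending can differ from those who do not, and can differ in different ways in each arm. Two features make arm-specific exclusion plausible here: participants know what they receive, and only the VR-SES arm has electrodes and current as a possible reason to miss or stop sessions.

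The rule governs the mFRT contrast, which is the trial's one confirmatory result, since the Discussion treats the secondary outcomes as exploratory. With about 11 per arm, one or two exclusions matter. The label adds to the problem: a reader of the results would take the analysis to be close to intention-to-treat.

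**Working it through.** **1. Consistency of the rule.**
- Threshold: 15/20 = 0.75 exactly. The smallest whole number of sessions above 75% of 20 is 16 (16/20 = 0.80). A participant with exactly 15 sessions is in by the bracketed count and out by the inequality.
- Against Adherence: that section invokes intention-to-treat for people who cannot finish their sessions. The analysis rule then removes those same people if they fall short of the threshold.
- Against the missing-data rule: most dropouts will have attended too few sessions and are out before imputation applies. Those left are people who attended enough sessions but missed T1. With only T0 and T1, carrying forward gives them their baseline value.

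**2. The plan's own sample size.** 20 × 1.10 = 22 matches the stated total; 20/0.90 = 22.2 would round up to 23. The base of 20 cannot be reproduced without an effect size.

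**3. Possible bias (assumptions, not document figures).** Let adherence propensity correlate r with the outcome, and let the lowest fraction p of adherents be dropped from one arm only. That arm's mean shifts by r·φ(z_p)/(1−p) SD, where z_p is the p-quantile of the standard normal.

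| Dropped from one arm | r = 0.3 | r = 0.5 |
|---|---|---|
| 2 of 11 | 0.097 SD | 0.161 SD |
| 3 of 11 | 0.137 SD | 0.228 SD |

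The formula is a large-sample one. A simulation of a null trial with 11 per arm (200,000 runs, two-sample t-test) gives slightly smaller shifts:

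| Dropped from one arm | Shift, r = 0.3 to 0.5 | Type I error (nominal 5%) |
|---|---|---|
| 2 of 11 | 0.09 to 0.15 SD | 5.5% to 6.4% |
| 3 of 11 | 0.13 to 0.21 SD | 5.8% to 7.4% |

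As an extreme bound, suppose those dropped are exactly the worst responders of one arm. The shift is then 0.30 SD (2 dropped) or 0.42 SD (3 dropped), and type I error is about 12% or 17%.

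**4. Power.** Solving the noncentral t for 10 per arm, 80% power and two-sided α 0.05 gives d ≈ 1.325. This is an assumption; a one-sided test would imply about 1.16. With noncentrality d·√(n₁n₂/(n₁+n₂)) and n₁+n₂−2 degrees of freedom:

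| Analysed | Noncentrality | Power |
|---|---|---|
| 11 v 11 | 1.325 × √5.5 = 3.11 | 84.0% |
| 10 v 10 | 1.325 × √5 = 2.96 | 80.0% |
| 9 v 11 | 1.325 × √4.95 = 2.95 | 79.6% |
| 8 v 11 | 1.325 × √4.63 = 2.85 | 76.7% |

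The one-arm exclusions of step 3 therefore cost little against the planned 80%. The 84% assumes that the effect is the same in everyone randomised.

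**The case against.** Several stronger readings are tempting, and the documents do not support them.

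- **Bias in favour of stimulation.** A reader might infer that people who cannot tolerate stimulation leave the VR-SES arm and that the VR arm has no matching route out. But the stopping rules cover both arms, and both do the same VR sessions. Stimulation is set to a comfortable level, and an extra week is allowed for making up sessions, so stopping and falling short is possible but not automatic. Unblinded VR participants who know that they lack stimulation might equally attend less. No passage links attendance to response. The direction is unknown.
- **Serious loss of power.** A reader might cite 75% (9 v 9) or 69% (8 v 8). Those figures need 4 or 6 of 22 excluded, split equally between arms, which is not the one-arm scenario behind the bias figures. Losing 2 or 3 of 11 in one arm already exceeds the planned 10%, and attrition and failed attendance will largely be the same people.
- **Imputation made impossible.** It is not: someone with enough sessions and no T1 value would still be imputed. The rule has little to act on, rather than nothing.
- **No other analysis exists.** The article is condensed, and sensitivity analyses may stand in a document not shown. Their absence is not the point.

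It is also fair to say that the article does not spell out what happens to a participant below the threshold who has a T1 value, and that it promises full reporting of missing data and CONSORT reporting. What stands is that the final analysis, as stated, requires a level of attendance. Reporting exclusions does not restore the randomised comparison.

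**Conclusion.** The point holds as a problem of set definition and labelling in the primary analysis. Followed as written, the rule conditions the mFRT comparison on post-randomisation attendance. It is inconsistent with the article's own intention-to-treat wording, leaves the imputation rule with few cases, and contains a threshold that contradicts itself by one session.

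The size is uncertain. Under the assumed correlation of 0.3 to 0.5 and one-arm exclusion, the shift is about 0.10 to 0.23 SD for 2 or 3 of 11 lost. That is roughly 8% to 17% of the back-solved effect (0.10/1.325 and 0.23/1.325). Exclusions balanced in number and kind would cause less bias between arms. Bias is the main concern; power is minor. Confidence is high on the definition and the contradictions, and low on the direction and size of any bias.

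**What to change.** - Make the primary analysis all randomised participants in their allocated arm, whatever number of sessions they attended, using every T1 value collected.
- Keep the attendance-based set only as a per-protocol sensitivity analysis under that name, with one stated threshold (15 or 16 sessions).
- Reconcile the Adherence wording, the analysis set and the missing-data rule, so that it is clear who is analysed and who is imputed.
- Report exclusions from the attendance set by arm and reason.

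The cost is rewording and reanalysis of data already held. The statistical downside is a somewhat diluted estimate if people with few sessions benefit less. Trial status says that the trial was completed in July 2025, so T1 values never collected from non-adherers cannot now be obtained. Their number by arm should be reported.

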## Discussion

The recovery of sitting balance is one of the primary and essential aims of rehabilitative programs in individuals with iSCI. Retraining sitting balance is challenging for healthcare professionals dealing with iSCI. The trial will provide information about the effectiveness of SES-augmented VR-based balance training in improving sitting balance and QoL in individuals with iSCI. The training is expected to enhance sitting balance and QoL in individuals with iSCI. To the best of our knowledge, no study until now has examined the effectiveness of SES-augmented VR-based training on sitting balance and QoL in the iSCI population.

This trial is designed to meet the methodological demand for adequate randomization, allocation concealment, and blinding of outcome assessors and statisticians. The trial will be reported according to the CONSORT guidelines. This study has several limitations. The recruitment of the participants will be done through a sample from one center; it may limit the generalizability of the findings. The sample size, calculated based on the primary outcome measure, may limit the power to detect differences in secondary outcomes. Therefore, secondary outcome findings should be interpreted as exploratory and hypothesis-generating. The lack of long-term follow-up may limit the ability to assess the durability of the intervention effects. In future, multi-center trials incorporating stratified block randomization are recommended to strengthen comparability.

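### With assessments only at T0 and T1, last observation carried forward copies the baseline and scores any analysed participant without T1 as exactly zero change

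*Protocol article*

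**What the plan says.** The legend to Table 2 describes two assessments. Baseline (T0) "will be done before group allocation", and "Post-intervention assessments of both groups (T_1_) will be done after 4 weeks of intervention". No visit between them is described. The Discussion rules out a later one: "The lack of long-term follow-up may limit the ability to assess the durability of the intervention effects".

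The Statistical analysis section then sets three rules that bear on this point:

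- **Missing data.** LOCF "will be applied in the case of missing data for dropped-out individuals". No other missing-data method and no sensitivity analysis is named.
- **Analysis set.** A modified intention-to-treat set in which "each participant must complete > 75% (15 of 20 sessions) of planned exercise sessions".
- **Between-group test.** If the data are normal, "we will analyze the intergroup comparison by applying a two-sample" t-test; if they are skewed, a Mann-Whitney U test.

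On expected losses, the Sample size section says: "The potential loss to attrition was estimated at 10" percent. The Adherence section promises a full report of the type, extent and pattern of missing data.

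**The concern.** LOCF presupposes at least one post-baseline value to carry. Here there is none, so it becomes baseline carried forward and fixes change at zero on the mFRT, the star test and the QoL items.

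Zero change is not a neutral value in this trial. Both arms train actively, the Background reports that game-based VR has improved dynamic sitting balance in SCI, and the Discussion expects improvement. Read literally, the attendance rule means that an imputed participant has completed about 15 or more of the 20 sessions, and so is an unlikely candidate for no response.

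The primary between-arm comparison is at stake. In an arm of 11, each imputed value is 1/11, or 9%, of the arm mean. It is also analysed as a real observation, so the standard error does not reflect the missing information.

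**Working it through.** **1. The plan's own figures.** The Sample size section gives 20 before attrition, 10% attrition and a total of 22. 20 × 1.10 = 22, which reproduces the total (20 / 0.90 = 22.2 would round up to 23). Planned attrition is thus about 2 of 22. The 20 cannot be rebuilt, because no effect size, SD or sidedness is stated. Solving back from 10 per arm, 80% power and a two-sided 5% t-test gives a standardised difference of 1.325. This is an assumption for what follows, not a figure in the plan. A one-sided test would give 1.16 to 1.23.

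**2. What LOCF does.** With T0 and T1 only, a missing T1 is replaced by T0, so change = T0 − T0 = 0.

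**3. Expected estimate.** Assume 11 per arm, SD of change 1, control mean change m, true difference d, and dropouts who would otherwise have responded like the rest of their arm. With a dropouts in VR-SES and b in VR:

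expected difference = ((11 − a)/11)(m + d) − ((11 − b)/11)m

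For d = 1.325:

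- One per arm: (10/11) × 1.325 = 1.20 for any m.
- Two in VR-SES: (9/11) × 1.325 − (2/11)m = 1.08, 0.90, 0.72 for m = 0, 1, 2.
- Two in VR: 1.325 + (2/11)m = 1.33, 1.51, 1.69.

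For d = 0 with two in VR: (2/11)m = 0, 0.18, 0.36, a spurious SES advantage.

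**4. Rejection rates.** Simulation, 100,000 trials per cell, two-sided t-test on change, dropouts set to 0:

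| Scenario | m = 0 | m = 1 | m = 2 |
|---|---|---|---|
| d = 1.325, no dropout | 84% | 84% | 84% |
| d = 1.325, one per arm | 78% | 72% | 59% |
| d = 1.325, two in VR-SES | 67% | 38% | 11% |
| d = 1.325, two in VR | 87% | 92% | 94% |
| d = 0, one per arm | 5.1% | 3.8% | 1.9% |
| d = 0, two in VR-SES | 4.9% | 6.2% | 8.5% |
| d = 0, two in VR | 5.0% | 6.4% | 8.6% |

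**5. Comparator.** Analysing only those with T1 gives 80.0% power at 10 and 10, and 79.6% at 9 and 11. The loss due to LOCF is measured from about 80%, not from the 84% that applies if nobody drops out.

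**6. If two dropouts fall at random across arms.** The chance that both are in VR-SES is 55/231 = 0.238, the same for VR, and 121/231 = 0.524 for one in each. Weighting the table:

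- Type I error stays at about 5% for every m (at m = 2: 0.238 × (8.5 + 8.6) + 0.524 × 1.9 = 5.1%).
- Power averages 78%, 69% and 56% for m = 0, 1, 2 (at m = 1: 0.238 × (38 + 92) + 0.524 × 72 = 69%).
- The average estimate is 1.20 SD.

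Dropout unrelated to arm therefore does not inflate the false-positive rate on average. It still attenuates the estimate, and the power cost grows with the improvement in both arms.

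**The case against.** The best case against the point concerns its reach and size, not its mechanism.

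**How many values are imputed.** A reader might infer that every dropout is scored as zero change. The documents do not support that. The attendance rule, read literally, removes early dropouts, so LOCF reaches only someone who attended enough sessions and then missed T1. Someone who stops training but attends T1 is not imputed at all. The Adherence section also allows an extra week to finish the sessions. With about 2 losses expected in 22, none or one imputed value is plausible. This limit stands. The article does not, however, reconcile the attendance rule with an imputation rule aimed at dropouts, and 15 of 20 is exactly 75%, not more than 75%, so the boundary is unclear too.

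**Type I error.** The 6% to 9% figures need both dropouts in one arm and improvement of 1 to 2 SD. At 0 to 0.5 SD the rate is 5.0% to 5.3%, and with one VR dropout it is about 5.0%. This also stands: a general inflation of type I error cannot be claimed.

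**Two further inferences fail.** One is that adding 10% for attrition contradicts imputing dropouts. It does not: the attendance rule removes some participants, and imputation restores no lost information. The other is that equal dropout always inflates the spread. With one zero among 11, the expected variance is 0.909 + 0.091 × (mean change)², which is 1.00 at a mean change of 1 SD and exceeds 1 only above that.

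**An unseen visit.** Repeated-measures ANOVA and Friedman's test are usually chosen for three or more time points, and the body of Table 2 is not shown. The text nevertheless names only T0 and T1, which is too firm to set aside on that hint.

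The promised report of missing data would show how many values were imputed. It would not correct the estimate.

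**Conclusion.** The point holds in its limited form. The schedule and the imputation rule, both stated in the article, together mean that an analysed participant without T1 is assigned exactly zero change, and the primary comparison treats that as data. This needs no outside assumption. Because the rule is fixed here, a separate analysis plan would have to overrule it rather than fill a gap.

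The size does rest on assumptions: 11 per arm, SD of change 1, a back-solved difference of 1.325 SD, control improvement of 0 to 2 SD, and the whole planned attrition of two participants falling among those analysed without T1. Under these, the estimate ranges from 0.72 to 1.69 SD against a true 1.325 SD, according to which arm loses participants. With one loss per arm, power is 78% to 59% against about 80% for complete cases. With no true effect and both losses in VR, the spurious advantage is 0 to 0.36 SD. If nobody in the analysed set misses T1 there is no effect, and if few do, it is small.

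**What to change.** Delete LOCF as the primary method. Analyse all observed T1 values in a linear model with treatment arm and the T0 value as terms. This is valid if, given arm and baseline, missingness does not depend on the unseen T1 value. Show baseline carry-forward only as a sensitivity analysis, with missing participants set to no change in one or both arms, so that readers can see whether the conclusion depends on it. State the number of analysed participants without T1 in each arm.

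The cost is about one sentence in the statistical section, a little programming and slightly fewer analysed participants. No new data are needed. Because the Trial status section says the trial was completed in July 2025, the change must be reported openly as made after data collection, with the LOCF result alongside it.
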